## Introduction

### Adult Weight Management

Small weight gains over time, around 1-2 pounds per year [1,2], contribute to the development of overweight and obesity. Once established, obesity is difficult to treat [3], as reduction of excess body weight is rarely effective in the long term. Short-term weight loss can be achieved by a variety of methods, but few of these approaches are sustainable and effective in facilitating permanent weight loss [4-10]. On average, individuals adhere to weight loss programs for approximately six months [11]; following weight loss, most individuals regain half of the weight lost within one year, and return to baseline weight within 3-5 years [11-13]. Weight gain prevention, on the other hand, avoids the difficulties that may accompany weight loss and its maintenance and offers an alternative option for weight management.

To reduce disease risk and improve overall health, effective weight gain prevention is essential; however, few interventions have successfully examined weight gain prevention and little is known about the determinants of and strategies for preventing weight gain over the long term. Much of the existing research has focused on treatment of overweight and obesity through reduction of excess body weight [14,15] or prevention of weight regain following weight loss [16-20].

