The Groningen Overweight and Lifestyle (GOAL) study examined weight gain prevention in overweight and obese men and women with hypertension and/or dyslipidemia in the Netherlands by comparing the effects of lifestyle counseling by a nurse practitioner to usual care from a general practitioner during a 1-year period [26]. No significant differences were observed in weight change between groups at one year or after three years [26,27]. Study of Novel Approaches to Weight Gain Prevention (SNAP) is the most recently published intervention [28]. Two novel self-regulation approaches to weight gain prevention—small consistent changes and large periodic changes—were compared to a minimal treatment control for an average of three years of follow-up. Results of this study have not yet been published [28]. Without complete knowledge of the determinants of and strategies for weight gain prevention, public health will remain at risk for complications and costs related to overweight and obesity. Weight gain prevention offers a primary strategy for weight management and obesity prevention [24,26].

Women who previously participated in a weight-loss intervention identified gender-specific life transitions and stressors, including pregnancy, post pregnancy, family responsibilities, health status changes, and aging as precipitators of weight gain [29]. Young adulthood and perimenopause appear to be critical intervals for weight gain [30-32]; therefore, weight gain prevention efforts should target these lifespan stages, specifically in women.

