## Methods

### Recruitment, Screening, and Enrollment

Participants were recruited by word-of-mouth, electronic mail messages, and posted flyers from the University of Illinois campus and the Urbana-Champaign (IL, USA) communities. A flow diagram of response, screening, and randomization steps is displayed in Figure 1. A total of 330 women responded to recruitment methods, between June and August 2014. Of these, 266 women met prescreening criteria (appropriate age, body mass index [BMI], and desire to prevent weight gain) and received screening materials including a medical history form, Zung Self-Rating Depression Scale/Status Inventory [33], and informed consent. A total of 146 women returned screening materials, which were reviewed by investigators. One hundred two women met eligibility criteria for participation, and 87 women were randomized, with 81 women completing baseline testing.

The current study included premenopausal women between the ages of 18-45 years with a BMI of >18.5 kg/m^2^. There were no additional criteria for body weight and BMI to ensure participation by women from a range of weight status categories. Further inclusion criteria included eumenorrhea (≥8 menstrual cycles/year), score of <50 on the Zung Self-Rating Depression Scale/Status Inventory [33], and no self-reported metabolic, cardiovascular or musculoskeletal diseases or use of medications or supplements to manage a chronic health condition. Exclusion criteria included women who currently smoked, were pregnant or attempting to become pregnant or were currently lactating. Women using medications influencing weight regulation, such as steroid or thyroid hormones or oral contraceptives, were excluded if use was for <2 months before the start of the study. Gastric bypass surgery was also an exclusion criterion.

The Institutional Review Board (IRB) for the protection of human subjects at the University of Illinois at Urbana-Champaign (UIUC) approved the study protocol (UIUC IRB#14397). Each participant provided written informed consent before study participation.

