### Statistical Analysis

Baseline characteristics of study participants were characterized using descriptive statistics: mean (SD). Participants in the three intervention groups (Treatment) will participate in five data collection sessions at specified intervals (Time). The Shapiro-Wilk test for normality will be used to test for normality and homogeneity of variance within groups; data will be transformed if necessary. Body weight, BMI, waist : hip ratio, FM, BF%, systolic and diastolic blood pressure, serum insulin, glucose, TC, HDL-C, LDL-C, TG, leptin, adiponectin, and resistin will be analyzed as dependent variables. Baseline variables that differ between groups will be included as covariates in the analysis. Dietary intake of macronutrients as estimated from 4-day food records, estimated energy expenditures, eating behaviors, health perceptions, and ratings of SCT mediators also will be compared among groups. A 3 x 5 (3 treatment groups x 5 time intervals) ANOVA with repeated measures on the time factor will be used to assess differences in outcomes within and between treatment groups over time. The group by time interaction will be examined for differences in time trend among intervention groups. Tukey pairwise comparisons will be used in conjunction with ANOVA to detect differences between treatment groups.

Some attrition is expected, as participants may be unable to comply with the intervention or may choose not to continue participation in the study. Participants who withdraw from the intervention will be asked to complete any remaining data collection sessions, and these data will be included in the statistical analyses (ie, intention-to-treat model). Data also will be analyzed using measurements only from those participants who complete all testing sessions. Statistical tests will be two-tailed with significance set at *P*<.01 to reduce the potential for Type I error. All statistical analyses will be conducted using Statistical Package for the Social Sciences (version 22.0, 2013, IBM Corp, Armonk, NY, USA).

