In a recent qualitative study of women who completed a weight-loss intervention conducted by a registered dietitian, women perceived the registered dietitian to be a credible source of nutrition information and found lack of access to a registered dietitian following completion of the intervention to be a barrier to weight-loss maintenance [29]. As a credible source of nutrition information [37], registered dietitians have a specialized skill set to support and encourage sustainable behavior changes to achieve weight management. Registered dietitians are generally regarded as the experts in weight management, but no studies have compared registered dietitians to other health professionals in the delivery of weight management information. The current study will fill this scientific gap by testing the ability of the registered dietitian to promote weight gain prevention as compared to an untrained professional. If registered dietitians are more effective in promoting weight gain prevention, these findings will support the notion that registered dietitians should be at the forefront in helping individuals attain successful weight management.

Women in the qualitative study [29] identified social support, basic nutrition education, accountability to others, self-motivation, mindfulness and awareness of food choices, planning ahead, portion control, and exercise as facilitators to weight loss and weight-loss maintenance while health status changes, environmental pressures, life transitions, absence of social support, lack of accountability, and internal factors were perceived as barriers. Additionally, women expressed their desire for continual contact with the registered dietitian as well as the group support offered by the education sessions [29].

Although there is no standardized definition of weight gain prevention or weight maintenance, a weight change of ±3% from baseline weight will be considered successful weight gain prevention. A 3% change criterion allows for normal day-to-day fluctuations that may result from measurement error, clothing, food consumption, and/or fluid balance [54].

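### The rule that keeps all data after withdrawal makes no exception for a pregnancy that begins during the trial, so gestational and postpartum measurements would be analysed as intervention outcomes

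*Protocol article*

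**What the plan says.** Three parts of the protocol article bear on this.

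- **Eligibility** (Recruitment, Screening, and Enrollment). "The current study included premenopausal women between the ages of 18-45 years", and they had to be eumenorrheic. Women were excluded if they "were pregnant or attempting to become pregnant or were currently lactating". This applies at entry; the article gives no rule for a pregnancy that starts later.
- **Analysis sets** (Statistical Analysis). "Participants who withdraw from the intervention will be asked to complete any remaining data collection sessions". Of the measurements obtained in this way, the article then says that "these data will be included in the statistical analyses (ie, intention-to-treat model". The second set is defined by attendance alone: "Data also will be analyzed using measurements only from those participants who complete all testing sessions". Neither sentence has an exception.
- **What counts as success** (Discussion, Principal Findings): "a weight change of ±3% from baseline weight will be considered successful weight gain prevention".

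The introduction (Weight Gain Prevention) reports that women in an earlier weight-loss intervention named life transitions and stressors, "including pregnancy, post pregnancy, family responsibilities, health status changes, and aging as precipitators of weight gain".

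**The concern.** By excluding pregnant and lactating women at entry, the trial already treats weight in those states as unsuitable for its question. The same states can arise within the 12 months, and the analysis rule then accepts the measurements without distinction. A woman who conceives, leaves the sessions and keeps attending visits is covered by the rule on data after withdrawal. One who conceives and attends every visit is in both analysis sets. In either case her weight, BMI, fat mass and serum markers at later visits reflect pregnancy or the postpartum period but are read as effects of her assigned arm.

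At stake is the comparison of weight over time between small arms, where one or two very large changes carry real influence. They widen the error variance, and if they fall in an intervention arm they hide a benefit. If the rule is settled only after results by arm are known, the handling of one or two influential women becomes a post hoc choice.

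**Working it through.** The article gives no sample-size calculation, target effect or SD of weight change, so there is no design figure to reproduce. Inputs marked *assumed* are not in the article.

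**1. Arm size.** 81 women completed baseline testing. The Results section reports 49 women (89%) still enrolled in the two intervention groups: 49/0.89 = 55.06, so 55 women, or about 27-28 per intervention arm. Control has 81 - 55 = 26. I use 27.

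**2. Reference size.** The Introduction gives "Small weight gains over time, around 1-2 pounds per year". At 0.4536 kg per lb this is 0.45-0.91 kg. It is a background rate, used here only as a yardstick.

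**3. Shift of an arm mean from one pregnancy** = extra weight / n, with 8-12 kg at the visit (*assumed*):

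| Extra weight | Shift, n = 27 | Share of 0.454 kg (1 lb) | Share of 0.907 kg (2 lb) |
|---|---|---|---|
| 8 kg | 8/27 = 0.30 kg | 65% | 33% |
| 12 kg | 12/27 = 0.44 kg | 98% | 49% |

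An earlier pregnancy counts for less: 5 kg gives 5/27 = 0.19 kg, which is 41% of 1 lb and 20% of 2 lb. Only visits after conception are affected.

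**4. Individual success criterion.** 3% of the mean baseline weight is 0.03 × 76.1 = 2.28 kg. A woman of average weight who gains more than that through pregnancy is outside the band.

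**5. Added variance.** One woman displaced by g kg raises the expected sample variance of change in her arm by g²/n. For 12 kg this is 144/27 = 5.3 kg². With an SD of change of 4 kg (*assumed*), the arm SD becomes √(16 + 5.33) = 4.6 kg. The standard error of a two-arm difference goes from √(32/27) = 1.09 kg to √(37.33/27) = 1.18 kg, about 8% wider.

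**6. Could it produce a false positive?** With an SD of change of 3-5 kg (*assumed*), the standard error of a difference is SD × √(2/27) = 0.82-1.36 kg. A simple two-sided comparison at P<.01 needs about 2.2-3.6 kg. One pregnancy shifts the difference by 0.30-0.44 kg (0.2-0.5 standard errors). Two in the same arm shift it by 16/27 = 0.59 to 24/27 = 0.89 kg. Both are well short.

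**7. How likely is a case?** If 2-5% conceive in 12 months (*assumed*), 81 × 0.02 = 1.6 to 81 × 0.05 = 4.1 conceptions are expected. If half of these are advanced enough by a visit to carry the gain in step 3 (*assumed*), the chance of at least one is 1 - 0.99^81 = 56% to 1 - 0.975^81 = 87%.

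**The case against.** The strongest reply is that this is an omission rather than an error. The sentence on data after withdrawal is ordinary intention-to-treat practice and does not mention pregnancy. A condensed article may leave incident pregnancy to the full protocol. That stands in part: a reader might infer that the plan deliberately scores pregnancy as failed prevention, and the article does not say so. The ±3% criterion appears only in the Discussion and is not among the listed analyses. But the inclusion rule is printed without qualification, and so is the completers rule; applied as they stand, they give the result described.

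Three further inferences are tempting and are not supported:

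- That one pregnancy is about as large as the effect the trial seeks. No such effect is stated, and against 2 lb the assumed 8-12 kg amounts to only 33-49%.
- That such a case is nearly certain. At 2-5%, the chance of at least one conception of any timing is 81-98%, but a late conception cannot produce 8-12 kg by month 12. Excluding women who were trying to conceive also lowers the rate.
- That one or two pregnancies could create a significant difference. Step 6 shows they fall well short at P<.01, and the added variance makes a false positive less likely.

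It is also fair to say that setting post-conception values to missing is a choice. Including everything is a legitimate treatment-policy analysis. It answers a different question, however, from the one implied by the entry exclusion. Intention-to-treat requires each woman to be kept in her randomized arm; it does not require gestational weight to be read as an outcome of the intervention.

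**Conclusion.** The point holds in limited form. The stated analysis sets admit measurements taken during and after a pregnancy that begins in the trial, against the logic of the trial's own entry exclusion. Under the assumed 8-12 kg, one advanced pregnancy moves an arm mean by 0.30-0.44 kg at the affected visits, roughly one third to all of the cited 1-2 lb yearly gain. The consequence to expect is lost precision and possible masking of a difference, not a spurious finding.

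The chance of at least one such case among 81 women is about 56-87%. It rests on two assumptions, that 2-5% conceive and that half of these are advanced by a visit. The arm size is derived from the article; the weight gain, the conception rate and the SD of change are not in it. The change is worth making because the rule is explicit and the remedy is cheap.

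**What to change.** Amend the Statistical Analysis section before outcomes are compared by arm:

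1. Record pregnancy status and estimated conception date at each visit.
2. In the main analysis, set weight, body composition and biochemical values after conception to missing, by the same rule in all three arms.
3. Replace the repeated-measures ANOVA with a likelihood-based mixed model for repeated measures. Conventional repeated-measures ANOVA drops a woman with any missing visit; the mixed model keeps her earlier visits and her randomized arm.
4. Add a sensitivity analysis that includes the post-conception values.
5. Report the number of pregnancies per arm.

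Cost: one item on the visit form, a few sentences in the plan and a change of model. A few post-conception values leave the main analysis, including any after an early loss. For those women the main analysis relies on a missing-at-random assumption, which the sensitivity analysis lets the reader set against the include-all result.

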## Results

Eighty-one women completed baseline testing. Baseline descriptive characteristics of the sample are displayed in Tables 1 and 2. Overall, these women were highly educated, with a majority of participants having at least a 4-year college degree. The racial/ethnic breakdown was reflective of the larger population, with non-Hispanic whites representing the majority. Age range was 18-45 years, and BMI range was 18.5-49.6 kg/m^2^. On average, participants were overweight and normotensive. Participants have been recruited, enrolled, and randomized to one of the three intervention groups. Education sessions will continue through August 2015, and results are expected by early 2016.

After 8 weeks, the halfway point for weekly education sessions, 75 (93%) of the original sample remained in the study. For those randomized to the two intervention groups, 49 (89%) women were still enrolled.

**Table 1 table1:** Baseline characteristics of women (n=81) participating in a 12-month weight gain prevention intervention and completing baseline testing.

Characteristic	All participants mean (SD)
Age (years)	31.4 (8.1)
Height (cm)	165.2 (5.9)
Weight (kg)	76.1 (19.0)
Body mass index (kg/m^2^)	27.9 (6.8)
Waist circumference (cm)	83.3 (13.6)
Hip circumference (cm)	110.7 (14.6)
Waist: hip ratio	0.8 (0.1)
Body fat (%)	34.6 (9.1)
Fat mass (kg)	27.9 (14.2)
Fat free mass (kg)	48.2 (5.4)
Systolic blood pressure (mmHg)	106.2 (11.0)
Diastolic blood pressure (mmHg)	70.9 (9.9)
Resting heart rate (bpm)	65.8 (6.0)

**Table 2 table2:** Demographic and education characteristics of all women (n=81) randomized to all groups.

Characteristic		All participants No (%)
**Education**		
	High school graduate	2 (3)
	Some college	15 (18)
	2-year associate degree/graduate	2 (3)
	4-year college degree/graduate	21 (26)
	Some graduate school	8 (10)
	Master’s degree	27 (33)
	Doctorate degree	6 (7)
**Race/ethnicity**		
	White, non-Hispanic	53 (66)
	Black, non-Hispanic	10 (12)
	Asian	8 (10)
	Non-white Hispanic or Latino	4 (5)
	Other (including multiracial)	6 (7)
**Total annual household income**		
	<$15,000	7 (9)
	$15,000 - $49,999	30 (37)
	$50,000 – $99,999	25 (31)
	>$100,000 – $199,999	18 (22)
	No response	1 (1)

## Discussion

### Principal Findings

The importance of weight gain prevention and maintenance of current weight has recently been recognized by the American College of Sports Medicine [18] and Healthy People 2020 [46] as critical; yet, there are currently no treatment guidelines for weight gain prevention. The gap in the understanding of the determinants, facilitators, and barriers to weight gain prevention likely exists due to the limited number of studies addressing prospective weight changes in adulthood. Awareness and identification of the determinants of weight gain prevention are necessary in order to increase the practicality of weight gain prevention for managing obesity.

While it may seem counterintuitive to promote weight gain prevention in overweight and obese individuals rather than weight loss, weight gain prevention is relevant for individuals of all BMI categories [47]. Preventing weight gain over time offers the opportunity to slow the progression of overweight and obesity and to avoid further exacerbations related to excess body weight in individuals who are already overweight or obese [48]. Additionally, weight gain prevention may require less intensive treatment than that required to achieve weight loss [2], and may be more successful in the long term as it avoids the problems associated with weight loss and its maintenance [27]. Weight maintenance, regardless of whether an individual is normal weight, overweight or obese, may be more beneficial and practical than repeated, minimally successful weight-loss attempts. While modest weight losses of 5-10% of body weight have significant effects on risk factors of disease, these benefits may be ameliorated with weight regain. Even with weight loss, metabolically healthy obese individuals may not show improvement in health outcomes, and weight loss in these individuals may promote weight cycling, or periods of weight loss followed by weight gain, which may have detrimental effects on mental, metabolic, and psychological outcomes [48-52]. Further, the adverse effects associated with weight cycling may be as harmful as maintenance of a high “unhealthy” body weight [51]. However, a recent study by Mason and colleagues [53] found that weight cycling was not associated with negative metabolic outcomes and a history of weight cycling was not related to the ability to lose and successfully maintain weight in the long term.

In a recent qualitative study of women who completed a weight-loss intervention conducted by a registered dietitian, women perceived the registered dietitian to be a credible source of nutrition information and found lack of access to a registered dietitian following completion of the intervention to be a barrier to weight-loss maintenance [29]. As a credible source of nutrition information [37], registered dietitians have a specialized skill set to support and encourage sustainable behavior changes to achieve weight management. Registered dietitians are generally regarded as the experts in weight management, but no studies have compared registered dietitians to other health professionals in the delivery of weight management information. The current study will fill this scientific gap by testing the ability of the registered dietitian to promote weight gain prevention as compared to an untrained professional. If registered dietitians are more effective in promoting weight gain prevention, these findings will support the notion that registered dietitians should be at the forefront in helping individuals attain successful weight management.

Women in the qualitative study [29] identified social support, basic nutrition education, accountability to others, self-motivation, mindfulness and awareness of food choices, planning ahead, portion control, and exercise as facilitators to weight loss and weight-loss maintenance while health status changes, environmental pressures, life transitions, absence of social support, lack of accountability, and internal factors were perceived as barriers. Additionally, women expressed their desire for continual contact with the registered dietitian as well as the group support offered by the education sessions [29].

Although there is no standardized definition of weight gain prevention or weight maintenance, a weight change of ±3% from baseline weight will be considered successful weight gain prevention. A 3% change criterion allows for normal day-to-day fluctuations that may result from measurement error, clothing, food consumption, and/or fluid balance [54].

